### Planned interventions

Baseline clinical assessmentNeurological diagnosis and medical historyMedication reviewDipstick urinalysis to screen for urinary tract infection (specifically evaluating for presence of nitrites)Nocturia assessment tool (ICIQ-N)Women of childbearing potential must have a negative urinary pregnancy test at screening (before the first study drug intake) & must agree to use a reliable method of contraception from the screening visit until 4 weeks after study drug discontinuation. Acceptable methods of birth control during participation in the study include: oral contraceptives, patch contraceptives, injection contraceptives, male condom with spermicide, diaphragm or cervical cap with spermicide, vaginal contraceptive ring, intrauterine device, surgical sterilization (bilateral tubal ligation), vasectomised partner(s) or total sexual abstinence.The MeNiMS co-ordinating centre will be notified if a subject becomes pregnant during the study, or changes her method of contraception

A woman is considered to be of childbearing potential unless she meets one of the following criteria: Previous bilateral salpingo-oophorectomy or hysterectomy, premature ovarian failure confirmed by a gynaecologist, aged >50 years and not treated with any kind of hormone replacement therapy for at least 2 years prior to screening, with amenorrhea for at least 24 consecutive months prior to screening, and a serum follicle stimulating hormone (FSH) level of >40 IU/L at Screening.

### Outcome measures

Primary outcome measure: Reduction in nocturia episodes per night, derived from a frequency volume chart (FVC). Analysis will be undertaken to assess the mean reduction in mean nocturia episodes. Reduced episodes of nocturia/night signifies improved sleep disturbance; 0.5/night fewer is clinically significant in older men [7]; this number may be different in MS, a condition in which there can be diverse causes of sleep disturbance.

Secondary outcome measures;Improved quality of life; assessed with the MS Quality of Life Index (MSQLI) [14], a disease-specific tool to capture comprehensive quality of life dimensions, including: fatigue, urinary symptoms and general function.Safety. MS disease severity at three key trial stages (before and at the end of each of the treatment periods) will be catalogued by assessing the MS-specific Expanded Disability Status Scale (EDSS) [15], the only outcome rating for MS disability accepted by Regulatory Authorities. Adverse events including MS relapses will also be documented.Urinary tract symptoms; response of LUTS to melatonin treatment will be evaluated using tools of the International Consultation on Incontinence Questionnaire (ICIQ). ICIQ-MLUTS and ICIQ-FLUTS are gender specific tools for assessing severity and bother of all LUTS [16]. Nocturia-specific tools are also available within ICIQ [17]. The ICIQ-N is a short tool, which will be used in screening and at the end of the crossover washout to catalogue subjective severity. Since the ICIQ-N questions are present verbatim in ICIQ-MLUTS and FLUTS, ICIQ-N will not be co-administered with the general LUTS tools at baseline and ends of the treatment phases. ICIQ-NQoL is a nocturia-specific quality of life tool which will be used throughout the study.Voided volume; the FVC will evaluate total overnight voided volume (by the standardised criteria [13]); mean voided volume will be derived by dividing total nocturnal voided volume by the number of nocturnal voids. Post void residual (PVR) will be checked during clinical assessment, with retesting during the study if clinically indicated.Sleep quality; measured with the Pittsburgh Sleep Quality Index (PSQI) [18].Partner’s sleep disturbance; impact of nocturia on bed-sharing partners is under-recognised. We will seek permission from study subjects to approach partners, in order to invite them to undertake qualitative interview regarding impact of nocturia on partners. This will be used to inform design of a partner-specific tool (akin to that developed for partners of men with prostate enlargement [19] for subsequent nocturia research.Cognition sub-study; performance on the minimal assessment of cognitive function in MS (MACFIMS), which is an objective, internationally validated tool for specific evaluation of several key domains of cognitive function specifically affected in MS [20] and features the three key tests of the BICAMS which is undergoing international validation as the newest cognitive outcome measure for translational inquiry.

### Qualitative assessment

Qualitative Interviews will be undertaken and analysed using standard thematic methods, to capture key issues from the patient/partner perspective. Qualitative interviews will be carried out after the final treatment phase, undertaking a thematic analysis to explore issues of quality of life, mechanisms of sleep disturbance, coping strategies, impact on partners, and aspects of participating in a study. Specific aims will be to;Explore the patients’ perspective of nocturia.Explore perceptions of the intervention on nocturia and associated quality of life impact from patients’ perspective.Evaluate the validity of the ICIQ-NQoL in the MS population.Where possible partners will also be interviewed on the above perspectives to explore wider impact.

Semi structured interviews will be recorded and analysed for emerging themes, with double coding of transcripts. Sufficient interviews will be undertaken to achieve saturation of emerging themes. Qualitative interviews will be carried out after the second treatment phase has been completed. Subjects will be able to opt out of participating in the qualitative assessment; a separate consent for qualitative assessment interview will be obtained. We will ask subjects for permission to undertake qualitative assessment with partners; if allowed to approach the partner, a separate consent for qualitative assessment interview will be obtained from the partner. The study flowchart is given in (Table 1).

**Table 1 Tab1:**
[figure not shown]
Study Flowchart

### Withdrawal criteria

A study subject will be discontinued from participation in the study if:Any clinically significant Adverse Event (AE) as evaluated by the PI, laboratory abnormality, intercurrent illness, or other medical condition or situation occurs such that continued participation in the study would not be in the best interest of the subject.The subject meets any exclusion criterion (either newly developed or not previously recognized).

Subjects are free to withdraw from participation in the study at any time upon request. Subjects who withdraw from the study will be followed up clinically as part of normal clinical care. Patients who withdraw as a consequence of Adverse Events will be followed up by the Study for 3 months and remain under clinical management thereafter if indicated. Safety data will be collected on any subject discontinued because of an AE or Serious Adverse Event (SAE) for a period of 3 months. Every effort will be made to undertake protocol-specified safety follow-up procedures under medical supervision until the symptoms of any AE resolve or the subject’s condition becomes stable. If voluntary withdrawal occurs, the subject will be asked to continue scheduled evaluations, complete an end-of-study evaluation, and be given appropriate care. All trial data to date will be held securely as per study subjects completing the protocol.

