## Background

Normal urinary function shows a circadian (day/night) cycle, with reduced urine production and bladder excitability during sleep. Nocturia is the symptom of needing to wake up to pass urine. It is caused by increased bladder excitability, impaired salt/fluid handling and endocrine causes.

Nocturia is common; overall prevalence of nocturia is substantial, and progresses in severity with ageing [1]. Nocturia is highly prevalent in neurological disease. Mild nocturia (1 episode per night) may be regarded as a “nuisance” symptom, of minor importance. However, if there are other reasons for sleep disturbance, as is common in multiple sclerosis (MS) [2], the additional episode of sleep disturbance from nocturia becomes more important for the person affected.

Moderate-to-severe nocturia profoundly affects quality of life as a consequence of fatigue, which results from the shortening of overall sleep duration and disruption of the phases of sleep (loss of the restorative phase). More importantly, severe nocturia is associated with major health problems [3]. The condition is thus important personally (impaired quality of life from fatigue), economically (impaired function affecting employment; for disabled or elderly people, need for additional care and reduced ability to maintain independent living at home) and clinically (association with major health issues).

Standard treatment comprises controlling fluid intake, timed diuretics, desmopressin, antimuscarinic drugs or bedtime sedatives/miscellaneous compounds [4]. Nocturia can be multifactorial, and a range of interventions is needed to individualise treatment selection and have the best chance of ameliorating symptoms. Current options can have side effects- which are common with antimuscarinics (dry mouth, constipation, swallowing difficulty, cognitive impairment), and sedatives (confusion, sedation hangover). Serious complications include; hyponatraemia (salt depletion/dilution) with diuretics/desmopressin, and acute retention of urine with antimuscarinics. Perceived poor efficacy and the safety concerns mean that clinicians may fail to evaluate fully or feel reluctant to instigate treatment; as a consequence, even severe nocturia symptoms may be left untreated.

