### Study setting and participants

This trial will recruit multiple sclerosis patients from North Bristol NHS Trust. Eligible subjects must be over 18 years of age with a confirmed neurological diagnosis of MS and least 1 episode of nocturia (as defined by International Continence Society criteria [13]) every night. In addition female subjects of child-bearing potential must agree to use an effective method of contraception throughout the study.

Subjects will be excluded if they i) are pregnant, ii) have a symptomatic urinary infection or iii) indwelling catheter, iv) use prescription/non-prescription sleeping tablets or Melatonin, v) use desmopressin or investigational medical compounds in the month preceding randomization vi) take antimuscarinic or diuretic medication, unless used long-term prior to study (at least 3 months) and continued at same dosing regime throughout the study, vii) have Diabetes mellitus or Diabetes insipidus.

All subjects will provide informed written consent prior to involvement in the study. The NRES Committee South West – Exeter have approved the study protocol (REC reference number: 12/SW/0322). A request for a clinical trial authorisation was accepted by the UK MHRA (reference; 18524/0222/001-0001). The study is registered in the BioMed Central ISRCTN Registry (http://www.isrctn.com/ISRCTN38687869).

Any protocol modifications that become necessary during the course of the trial will be discussed with all relevant parties in advance.

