### Statistics and data analysis

Sample size is informed by (a) a previous study of melatonin, which showed a reduction in nocturia episodes of 0.5 per night to be clinically significant [7], (b) comparable crossover investigations using melatonin in other populations [21], (c) crossover trial methodology [22], and (d) project feasibility. For a two-sided test, using standard levels of statistical significance (alpha = 0.05), a sample size of *n* = 21 complete data sets would have 80% power to detect a medium to large effect size (Cohen’s d = 0.65) with 80% power, and a sample size of *n* = 34 would be needed for a medium effect size (Cohen’s d = 0.5).

The balanced two group, two period, two sequence, double-blind, randomised crossover design with wash-out period comparing treatment to control, ranks highly in the hierarchy of designs. The analyses of the resultant data under this AB/BA design may proceed using well known statistical techniques (e.g. [23]).

Primary analyses will focus on nocturia episodes per night and volume voided per night determined pre- and post-treatment for the two conditions (melatonin, placebo) within each period. The experimental structure therefore has a two by two fully repeated measures structure. The design has been structured with a large washout period and it is anticipated that there will be no carryover effects on physiological and psychological outcomes. This assumption will be tested. Period effects should also be absent and this supposition will also be tested and analysis will proceed to estimate treatment effects robust to any period effect (CROS analysis). It is recognised that outcome data may be skewed for this population and nonparametric or bootstrapped inference will be used as appropriate. Analyses will proceed on an Intent-to-Treat basis.

A missing data analysis will also be performed and sensitivity of statistical conclusions to missingness will be undertaken using standard imputation techniques. Data integrity checks will be undertaken prior to inferential analysis including a detailed graphical and summary statistics descriptive analysis. The statistician will be masked to prevent ascertainment bias. All analyses, and the reporting of analyses, will be undertaken in the spirit and guidance of the CONSORT guidelines.

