### Regulatory issues

Eudract Reference: 2012-004183-21 has been used for UK competent authority (MHRA) forms in order to get clinical trial authorization

Consent to enter the trial will be sought from each participant only after a full explanation has been given, an information leaflet offered and time allowed for consideration. Signed participant consent will be obtained. The right of the participant to refuse to participate without giving reasons will be respected. After the participant has entered the trial the clinician remains free to give alternative treatment to that specified in the protocol at any stage if he/she feels it is in the participant’s best interest, but the reasons for doing so will be recorded. In these cases, the subjects will remain within the trial for the purposes of follow-up and data analysis. All subjects will be free to withdraw at any time from study without giving reasons and without prejudicing further treatment.

Where possible we will gain consent from study subjects to approach partners, in order to invite them to undertake qualitative interview regarding impact of nocturia on partners and gain their consent.

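### The withdrawal rule ends study participation when any exclusion criterion is newly met. This conflicts with the retention rule for patients given alternative treatment and undercuts the intent-to-treat analysis.

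*Protocol article*

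**What the plan says.** All references are to the protocol article.

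- **Withdrawal criteria.** The list opens with "A study subject will be discontinued from participation in the study if", and one of its two triggers is "The subject meets any exclusion criterion (either newly developed or not previously recognized". What ends is study participation. The rule is mandatory and covers every exclusion criterion.
- **Study setting and participants.** The exclusion criteria include "have a symptomatic urinary infection or iii) indwelling catheter, iv) use prescription/non-prescription sleeping tablets or Melatonin" and also "take antimuscarinic or diuretic medication, unless used long-term prior to study (at least 3 months) and continued at same dosing regime throughout the study". All of these can arise after randomisation.
- **Background.** "Standard treatment comprises controlling fluid intake, timed diuretics, desmopressin, antimuscarinic drugs or bedtime sedatives/miscellaneous compounds". Several exclusion criteria are therefore treatments that a patient with bad nocturia might be given.
- **Regulatory issues.** The clinician may depart from protocol treatment at any stage in the participant's interest. The consequence is: "In these cases, the subjects will remain within the trial for the purposes of follow-up and data analysis".
- **Statistics and data analysis.** "Analyses will proceed on an Intent-to-Treat basis". Imputation is planned as a sensitivity analysis, and the sample size is counted in complete data sets.
- **Withdrawal criteria, on follow-up.** "If voluntary withdrawal occurs, the subject will be asked to continue scheduled evaluations". For discontinuation because of an adverse event, the section promises three months of safety data. For patients who withdraw in general, it refers to normal clinical care. Data already collected are kept.

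**The concern.** A patient whose nocturia or sleep is poor in one period is more likely to be given a sleeping tablet, an antimuscarinic or a diuretic, and the removal rule then ends that patient's participation. Infection or catheterisation changes night voids directly. In each case the later frequency volume charts may be lost for a reason tied to the primary outcome. If melatonin works, this would happen more often on placebo.

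Two things are at stake. First, site staff face two instructions that cannot both be followed for the same patient. Second, intent-to-treat needs outcomes from randomised patients whatever happens after randomisation. A rule that ends participation for post-randomisation events, or because ineligibility is found late, works against that. In a crossover the loss is costly, because a patient who leaves before the second-period chart provides no within-patient contrast.

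**Working it through.** **Step 1: set the rules side by side.**

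| Event after randomisation | Withdrawal criteria | Regulatory issues | Direct conflict? |
|---|---|---|---|
| Clinician gives a sleeping tablet | leaves the study | stays for follow-up and analysis | yes |
| Clinician starts or changes an antimuscarinic or diuretic | leaves the study | stays for follow-up and analysis | yes |
| Patient takes a non-prescription sleeping tablet unprompted | leaves the study | not addressed | no |
| Symptomatic urinary infection, new diabetes, pregnancy | leaves the study | not addressed | no |
| Ineligibility at entry found late | leaves the study | not addressed | no |

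The first two rows contradict each other outright. In the other three there is no clash with Regulatory issues, but the tension with intent-to-treat remains.

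**Step 2: who keeps giving outcome data?** The request to continue scheduled evaluations is written for voluntary withdrawal. The text has no matching provision for a patient discontinued by rule.

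**Step 3: reproduce the plan's sample size.** Inputs from Statistics and data analysis: two-sided alpha 0.05, 80% power, d = 0.65 or 0.5. For a period-adjusted AB/BA comparison, treat d as the mean within-patient difference divided by its SD. The noncentrality is λ = d√n, the degrees of freedom are n − 2, and power = P(|T| > t(0.975, n − 2)), where T is noncentral t with noncentrality λ.

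- d = 0.65, n = 21: λ = 0.65 × √21 = 2.979, critical value 2.093, power 0.807. At n = 20 power is 0.785, so 21 is the smallest n.
- d = 0.5, n = 34: λ = 0.5 × √34 = 2.915, critical value 2.037, power 0.807. At n = 33 power is 0.795, so 34 is the smallest n.

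Both stated sizes reproduce. There is no error in them.

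**Step 4: illustrate the cost of lost pairs.** The documents give no removal rate and no number to be randomised. Assume that 21 are randomised and that 10% or 20% lose their pair.

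- 21 × 0.9 = 18.9, so 19 pairs: power 0.761.
- 21 × 0.8 = 16.8, so 17 pairs: power 0.707.

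Conversely, ending with 21 complete sets would need 21/0.9 = 23.3, so 24 randomised, or 21/0.8 = 26.25, so 27.

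**Step 5: illustrate the direction of bias.** Assumptions, none from the documents: bivariate normal outcomes with SD 1, correlation 0.5 and true effect 0.65. The SD of the difference is then √(2 − 2 × 0.5) = 1, so the standardised effect is also 0.65. Remove every patient whose value in either period exceeds the placebo 90th or 85th percentile.

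- 90th percentile: about 11% removed, mean difference 0.58, standardised effect about 0.62.
- 85th percentile: about 17% removed, mean difference 0.56, standardised effect about 0.60.
- If only 30% of those above the threshold are removed: about 3% to 5% lost, standardised effect about 0.64.

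In this set-up the bias is toward no effect. It is material only when removal follows outcome closely.

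**The case against.** The strongest reply is that this is a condensed article whose visit schedule is not shown. Silence on charts after rule-based discontinuation is not a statement that charts stop. Data to date are kept, a missing-data analysis is planned, and the analysis set can be defined in a statistical analysis plan. All of that is fair, and it narrows the point. It does not remove it. Two stated rules give opposite instructions for the same patient, and an analysis plan cannot recover charts that were never collected.

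A reader might also infer more than the documents support:

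- *That the removal rule contradicts Regulatory issues as a whole.* It does so only where the criterion is met through alternative treatment. Infection, pregnancy, diabetes and late-found ineligibility are not addressed there.
- *That starting desmopressin triggers removal.* That criterion is worded for the month before randomisation, so later use does not literally meet it.
- *That the trial falls short of its stated power.* The 21 is already a count of complete data sets, and no recruitment target is given.
- *That every patient removed by rule drops out of the primary analysis.* The article names a treatment estimate robust to period effects but does not confine the primary set to completers. A patient removed after the second-period chart still has a contrast.
- *That the bias figures predict this trial.* They rest on an assumed link between removal and outcome.

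**Conclusion.** The concern holds in limited form. For sleeping tablets, and for new or changed antimuscarinics or diuretics given as alternative treatment, Withdrawal criteria and Regulatory issues cannot both be followed. More broadly, ending the participation of randomised patients by rule, while asking only voluntary withdrawals to continue evaluations, undercuts the stated intent-to-treat principle, and the resulting loss can depend on outcome.

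The conclusion rests on the wording and needs no figure. Its size in this trial is unknown. The power values in step 4 depend on assumed losses of 10% or 20% from 21 randomised patients, and the attenuation in step 5 depends on assumed removal at a threshold. Both are illustrations. The point should be settled in the protocol text, because outcome data not collected cannot be restored at analysis.

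**What to change.** Reconcile Withdrawal criteria, Regulatory issues and Statistics and data analysis by treating two decisions separately: discontinuing study drug, and ending outcome follow-up. The first is a clinical decision and is not addressed here. For the second, extend the existing request to continue scheduled evaluations (end-of-period frequency volume charts and questionnaires) to patients discontinued by rule, including those whose ineligibility is found late, subject to consent. State that they are analysed as randomised.

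Optionally, a mixed model with treatment, period and a random patient effect would let patients with one usable period contribute. It does not by itself remove bias from outcome-dependent loss, so continued outcome collection is the essential part.

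The cost is a wording change and a few extra charts and questionnaires from the existing schedule. Some values will be measured after other treatment has started, which an intent-to-treat comparison accepts.
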